### Ethical considerations

Before the intervention, each subject will be asked to sign a written informed consent. The study was approved by the ethics committee of the Shanghai University of Sport, China.

### Interventions

Both groups will receive exercise intervention twice a week for 3 months, and each session will involve a warm-up for 5 minutes and cool down for 5 minutes. The participants will be asked to fill out forms to record the times and durations of exercise intervention.

#### Intervention group

All subjects will perform whole body vibration exercise by an available vibration device (AV001; BODYGREEN, Taiwan, China). To eliminate any effect of vibrations, we ask patients to remove their shoes. The WBV exercise protocol includes five exercise positions: double leg stance, deep squat, lower back extension, bridge pose, and push up. More information about the WBV protocol is shown in Table 1 and Figure 2. WBV exercise programs will be led by registered physical therapists.

**Table 1 T1:** Protocol of whole body vibration (WBV) exercise

**Exercise positions**	**Each time (s)**	**Repetitions (n)**	**Frequency (Hz)**	**Interval rest (s)**	**WBV total time (s)**
Double leg stance	90	2	18	30	180
Deep squat	60	2	18	30	120
Lower back extension	90	2	18	30	180
Bridge pose	60	2	18	30	120
Push up	60	2	18	30	120

**Figure 2 F2:**
[figure not shown]
**Illustration of five movements. A**. Double leg stance: place the feet parallel on both sides of machine with heals turned slightly outward. **B**. Deep squat. **C**. Lower back extension. **D**. Bridge pose. **E**. Push up.

#### Control group

The participants in the control group will perform the same exercise protocol as the WBV group, but without vibration. The participants in the both groups will be asked to maintain their previous lifestyle and not take part in any other regular rehabilitation programs.

### Outcome measures

Primary outcome measures include the following:

1. Pain intensity, which will be assessed using the VAS. It is usually a horizontal line, 100 mm in length, which is marked with ‘no pain’ (score 0) and ‘unbearable pain’ (score 10) from the left to the right. The patient marks on the line the point that they feel represents their perception of their current state. The amount of pain that a patient feels ranges across a continuum from none to an extreme amount of pain [31].

2. Back function, which will be measured using the Oswestry Disability Index [32], an index that consists of ten sections related to activities of daily living commonly affected by low back pain. Each section is scored from 0 to 5 with higher values indicating more severe impact.

3. Adverse events associated with whole body vibration exercise, which will be reported.

Secondary outcome measures include:

1. Muscle strength and endurance of trunk, which will be tested using a Biodex 3 dynamometer (Biodex Medical Systems, New York, USA). Participants will perform ten maximum concentric contractions for trunk extensors and flexors at the angular velocities of 60°/s, 120°/s. The muscle endurance index is defined as the ratio of the work done during the last five contractions over the first five contractions. Main outcome parameters will be peak torque (Newton-meters), peak torque/ body weight, maximal power output (power) in Watts, work (work) in Joules [33].

2. Trunk proprioception, which will be assessed with a joint position matching test [24]. The subject’s trunk will be moved to reference position (flexion or extension), and maintained at the position for 3 s. Then the subjects will be asked to reproduce the reference position from the neutral position. The subject is instructed to stop a position when he or she thinks that the test position has been reached. The assessor records the position and angle. This sequence of events will be repeated three times, and these three measures were averaged for a score of repositioning error for the first pre-test. The large absolute error is considered as poor proprioceptive acuity.

3. Transversus abdominis activation capacity, which we will assess using the Stabilizer Pressure Biofeedback Unit (PBU, Chattanooga Group, Australia) [34]. The subject will be asked to lie in prone position over a rigid surface, then a PBU device will be placed under the transversus abdominis. The subjects are asked to contract the lower stomach for 10 seconds without moving the back or the hips. Then the assessor will record the pressure reduction from the PBU.

4. Quality of life, which will be assessed with the short form 36 (SF-36) health survey [35]. The SF-36 includes eight scaled scores: vitality, physical functioning, bodily pain, general health perceptions, physical role functioning, emotional role functioning, social role functioning, and mental health. A score of SF-36 is from 0 (worst) to 100 (best).

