**Methods/Design:**

We will conduct a prospective, single-blind, randomized controlled trial of 120 patients with chronic low back pain. Patients will be randomly assigned into an intervention group and a control group. The intervention group will participate in whole body vibration exercise twice a week for 3 months. The control group will receive general exercise twice a week for 3 months. Primary outcome measures will be the visual analog scale for pain, the Oswestry Disability Index and adverse events. The secondary outcome measures will include muscle strength and endurance of spine, trunk proprioception, transversus abdominis activation capacity, and quality of life. We will conduct intention-to-treat analysis if any participants withdraw from the trial.

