## Methods/Design

### Aim of the study

We will perform an RCT involving whole body vibration exercise in patients with chronic low back pain in order to determine:

1) whether WBV exercise is effective for the treatment of chronic LBP,

2) whether WBV exercise produces more beneficial effects than general exercise for chronic LBP, and

3) adverse effects associated with whole body vibration.

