### Withdrawal criteria and management

Patients with chronic LBP will be allowed or be asked to withdraw from the study if:

1. The patient makes such a request.

2. The patient develops a serious disease, such as stroke or heart disease.

3. The patient has an adverse effects related to the WBV exercise.

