### Statistical analysis

The SPSS 17.0 and Microsoft Excel 2007 software will be used to perform statistical analyses. Data will be expressed as mean?±?standard deviation (SD). We will use two-way repeated measures analysis of variance (group?×?time) to compare the effect of WBV exercise group with the control group, including the primary and secondary outcomes. If subjects are lost to follow-up, an intention-to-treat analysis will be conducted. A T-test will be used to compare the changes in measures within groups when the analysis of variance reveals a significant difference. Statistical significance is a *P* less than 0.05.

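### The third primary outcome counts only adverse events linked to vibration, so the matched control arm gives no comparison rate, and the stated ANOVA does not fit an event outcome

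*Protocol article*

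**What the plan says.** The Protocol article describes this outcome in several places, and the descriptions differ.

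- **Abstract, Methods/Design:** "Primary outcome measures will be the visual analog scale for pain, the Oswestry Disability Index and adverse events". No restriction by cause.
- **Outcome measures, third primary outcome:** "Adverse events associated with whole body vibration exercise, which will be reported". Restricted to vibration.
- **Aim of the study, third aim:** "adverse effects associated with whole body vibration". The same restriction.
- **Withdrawal criteria and management:** "The patient has an adverse effects related to the WBV exercise". The same restriction again.
- **Control group:** "The participants in the control group will perform the same exercise protocol as the WBV group, but without vibration".
- **Statistical analysis:** "We will use two-way repeated measures analysis of variance", with group and time as factors, "to compare the effect of WBV exercise group with the control group, including the primary and secondary outcomes". The same section opens with "Data will be expressed as mean" and SD. It makes no exception for adverse events and names no method for counts or proportions.

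**The concern.** The comparator is well chosen: both arms do the same five movements for the same time, and only vibration differs. The Strengths and limitations section presents this as an advantage. For safety, that advantage depends on counting events in the same way in both arms. Soreness or a pain flare from squats, bridges or push-ups can occur in either arm. Under the Methods wording it can qualify as an outcome in only one.

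The safety question matters here, because the Background notes that some consider vibration harmful. If only vibration-linked events are recorded, the WBV tally has no control rate beside it. Exercise-related events may then be read as vibration harm, or vibration harm may be set aside as ordinary exercise soreness.

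The second problem is the analysis. A repeated-measures ANOVA on means needs a score measured at each assessment. An event caused by the intervention has no value before the intervention begins.

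**Working it through.** The document gives no event rate, effect size or SD for this outcome, so there is no stated figure to reproduce. The check sets the passages together and then illustrates the size under assumptions.

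**Inputs from the document.** 120 patients (Study design) allocated 1:1, so 120/2 = 60 per arm. Assessments before intervention, at 3 months and at 6 months. Significance at P below 0.05; two-sided testing is my assumption.

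**Step 1: what each definition measures.** Let *e* be the risk of an event due to the shared exercises, equal in both arms, and *v* the added risk due to vibration. Let *a* be the share of exercise events in the WBV arm that are attributed to vibration, and *b* the share of true vibration events so attributed.

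- All events, both arms: (*e* + *v*) − *e* = *v*, the quantity of interest.
- Methods wording: the WBV arm records *a·e* + *b·v* and the control arm 0 by definition. Treated as a difference, the error is *a·e* − (1 − *b*)·*v*.

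The error can go either way. It depends on attribution, which the randomised comparison would not need.

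**Step 2: size when vibration adds nothing (*v* = 0; assumed rates).** With *e* = 15% and *a* = 1, the expected WBV tally is 0.15 × 60 = 9. With *a* = 0.5 it is 4.5, and with *a* = 0 it is 0. The true difference is zero throughout.

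**Step 3: chance of a spurious significant result.** The plan names no test for proportions, so I use Fisher's exact test only as a yardstick. Against 0/60, five events give p = 0.057 and six give p = 0.027, so six is the smallest significant count. The chance of reaching it is P(X ≥ 6) with X binomial (60, *a·e*).

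| Shared risk *e* | Same definition in both arms | Control fixed at zero, *a* = 1 |
|---|---|---|
| 5% | 0.0105 | 0.079 |
| 10% | 0.0218 | 0.563 |
| 15% | 0.0266 | 0.903 |
| 20% | 0.0282 | 0.988 |

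The last column is the worst case. At *e* = 20%, half attribution gives *a·e* = 10% and a chance of 0.563; quarter attribution gives 5% and 0.079.

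**Step 4: the ANOVA.** Take the mean number of qualifying events at a later time *t*. The group-by-time contrast is (WBV at *t* − WBV at baseline) − (control at *t* − control at baseline). Baseline is zero in both arms, since no one has yet exercised in the trial, and control is zero throughout by definition. The contrast reduces to WBV at *t*, with no variance in the control arm. It would test whether the WBV arm had any such events, not whether the arms differ in safety.

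**The case against.** The strongest reply is that the plan intends a descriptive list of harms. The comparison is in the second aim; the third aim is not written as one, and the outcome text says only that events will be reported. On that reading a list of events in the WBV arm meets the aim, and the ANOVA sentence covers only scored measures. The Abstract's unrestricted wording may also show that all events will be collected, and nothing says control events will go unrecorded.

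Much of this stands, and it rules out several stronger readings that a reader might infer:

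- **That the safety aim cannot be answered at all.** A descriptive list would answer it, though weakly on cause.
- **That events are attributed by someone who knows the arm.** The document says only that the trial is single-blind. It does not say who judges cause.
- **That the trial will report 9/60 against 0/60.** This needs full attribution and a control arm shown as a true zero. The document supports neither, and the Fisher test is not part of the plan.
- **That the 6.0% exact upper limit for zero events in 60 (1 − 0.025^(1/60) = 0.0596) shows the defect.** It reflects only the arm size and would be the same under any definition.

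The reply does not remove the problem. A descriptive list from one arm still cannot separate vibration from exercise. The Abstract and the Methods differ. The analysis sentence, as written, includes a declared primary outcome that it cannot handle. Nor is this detail left to a fuller document: the definition and the method are both stated, and a later analysis plan could not supply control events that were never collected.

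**Conclusion.** The point holds as a problem of definition and method. Followed as written, the Methods give no control-arm rate for a declared primary outcome, disagree with the Abstract on its scope, and assign it an analysis that does not fit. The conclusion rests on reading the vibration restriction as a link to cause. If it means only events observed during the programme, the wording still needs to say so for both arms.

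The numerical size is not determined by the document. In the illustration it ranges from nothing to a near-certain spurious difference, depending on the assumed event rate and share attributed. The VAS and ODI comparisons do not depend on this outcome. It should be fixed, but it does not undermine the efficacy part of the trial.

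**What to change.** 1. Reconcile the Abstract, the third aim and the third primary outcome by defining the outcome as all adverse events, recorded the same way in both arms whatever the judged cause.
2. Report the number and proportion of participants with at least one event in each arm, with a risk difference and 95% CI. Keep attribution to vibration as a descriptive column.
3. State in the Statistical analysis section that the repeated-measures ANOVA and the mean and SD summary do not apply to adverse events.

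The cost is small: a little more data collection on the exercise forms that both groups already complete (Interventions), and a few changed sentences. Timing matters because Trial status says recruitment is underway, and control-arm events not recorded now may not be recoverable. The restriction in the withdrawal criteria should be checked against the revised definition for consistency; this point takes no position on what that clinical rule should be.

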### Statistical analysis

The SPSS 17.0 and Microsoft Excel 2007 software will be used to perform statistical analyses. Data will be expressed as mean?±?standard deviation (SD). We will use two-way repeated measures analysis of variance (group?×?time) to compare the effect of WBV exercise group with the control group, including the primary and secondary outcomes. If subjects are lost to follow-up, an intention-to-treat analysis will be conducted. A T-test will be used to compare the changes in measures within groups when the analysis of variance reveals a significant difference. Statistical significance is a *P* less than 0.05.

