**Figure 1 F1:**
[figure not shown]
Flow diagram showing whole body vibration exercise for patients with low back pain (LBP).

All participants, prior to initiation of the study, will accept a questionnaire asking for the following details: basic information (for example, age), past and present job status, medical history, pain (visual analog scale, VAS), back function (Oswestry Disability Index, ODI) and exercise habits (for example, frequency and time/session). Prior to inclusion, informed consent will be sought from all participants in the study.

The subjects will be allocated in a 1:1 ratio by computer-generated randomization if they meet the inclusion criteria. After randomization, patients with chronic LBP will be assigned to the control group (general exercise) or to the intervention group (WBV exercise). The total study period will be 6 months, which has a 3-month intervention and 3-month follow-up period with no intervention. The study will include assessments at the following time points: before intervention, at 3 months, and at 6 months.

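### The arms are compared by an omnibus group-by-time ANOVA with neither the deciding term nor the visit named, and the only follow-up is within groups, so no between-arm estimate at 3 or 6 months is planned

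*Protocol article*

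**What the plan says.** All places are in the Protocol article.

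- Statistical analysis names a "two-way repeated measures analysis of variance", labelled group by time, as the tool "to compare the effect of WBV exercise group with the control group, including the primary and secondary outcomes".
- Study design gives the schedule: "assessments at the following time points: before intervention, at 3 months, and at 6 months". The 3-month visit closes the intervention. The 6-month visit follows 3 months with no intervention.
- Statistical analysis then states one follow-up: "A T-test will be used to compare the changes in measures within groups when the analysis of variance reveals a significant difference". The threshold is "Statistical significance is a *P* less than 0.05".
- Aim of the study, item 2, asks "whether WBV exercise produces more beneficial effects than general exercise for chronic LBP".

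The article does not say outright that baseline is a level of time. It describes no other use of the baseline value, so that is the natural reading. It does not say whether the group term or the interaction is the treatment test.

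**The concern.** A two-way repeated measures ANOVA produces two terms that involve group, and they answer different questions. The group main effect is the between-arm difference averaged over all three visits, including the one before treatment, where randomisation makes the expected difference zero. The interaction is a 2-df test that the between-arm difference is not constant across visits. Neither says at which visit the arms differ, and the two follow-up visits differ in kind: one is the end of treatment and the other is durability after treatment stops.

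The stated follow-up cannot fill the gap. A t-test of change within each arm does not compare the arms. One arm may change significantly and the other not without any demonstrated difference between them.

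At stake is whether the second aim gets a direct answer, that is, an estimated difference between arms at a known visit with its uncertainty. Depending on the term used, power in a trial of 120 patients is also at stake.

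**Working it through.** **Inputs from the article:** 120 patients allocated 1:1, so n = 60 per arm; three assessments; significance level 0.05.

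**Assumptions:** two-sided test; complete data; effect d = 0.5 SD at its peak; equal correlation ρ between visits, varied from 0.3 to 0.8. The article gives no effect size, SD, correlation or power, so there is no planned power figure to reproduce. For scale, 120 patients in a plain two-group comparison give 80% power for about 0.51 SD.

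Let e = (0, e₃, e₆) be the between-arm differences in SD units at baseline, 3 and 6 months, and ē their mean. Power comes from the noncentral F distribution.

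**1. Dilution if the group main effect is the test.** An effect D at both follow-ups gives ē = (0 + D + D)/3 = 2D/3. An effect at 3 months only gives ē = D/3. With D = 0.5 these are 0.33 and 0.17 SD.

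λ = (n/2)·ē² / [(1+2ρ)/3], df 1 and 118. At ρ = 0.5:
- both visits: 30 × 0.1111 / 0.6667 = 5.00, power 60%;
- 3 months only: 30 × 0.02778 / 0.6667 = 1.25, power 20%.

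**2. Interaction.** λ = (n/2)·Σ(e_t − ē)² / (1−ρ), df 2 and 236. For e = (0, 0.5, 0.5), Σ = 0.1667. At ρ = 0.5, λ = 30 × 0.1667 / 0.5 = 10.0, power 81%. The pattern (0, 0.5, 0) has the same Σ and the same power. Two quite different courses are therefore equally likely to give a significant result, and the test cannot tell them apart.

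**3. Baseline-adjusted contrast at 3 months (ANCOVA).** λ = (n/2)·e₃² / (1−ρ²), df 1 and 117. At ρ = 0.5, λ = 30 × 0.25 / 0.75 = 10.0, power 88%.

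**4. Range of settings**

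| Effect at 3 / 6 months (SD) | ρ | Group term | Interaction | ANCOVA at 3 months |
|---|---|---|---|---|
| 0.5 / 0.5 | 0.3 | 70% | 66% | 81% |
| 0.5 / 0.5 | 0.5 | 60% | 81% | 88% |
| 0.5 / 0.5 | 0.7 | 53% | 96% | 97% |
| 0.5 / 0.5 | 0.8 | 49% | 99.6% | 99.5% |
| 0.5 / 0.25 | 0.5 | 38% | 68% | 88% |
| 0.5 / 0.25 | 0.7 | 33% | 89% | 97% |
| 0.5 / 0 | 0.5 | 20% | 81% | 88% |
| 0.25 / 0.5 | 0.5 | 38% | 68% | 35% |
| 0.25 / 0.5 | 0.7 | 33% | 89% | 48% |

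Simulation of 4,000 trials at ρ = 0.5 agrees: 60%, 80% and 87% for an effect at both visits, and 20%, 82% and 88% for an effect at 3 months only. If 15% are lost (51 per arm), the order is the same: interaction 74%, ANCOVA 82% for 0.5 SD at both visits and ρ = 0.5.

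**5. Type I error if either term were accepted.** The two tests are close to independent, so 1 − 0.95² = 9.75% for one outcome. Null simulations gave 9.6% to 10.1%.

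**The case against.** The strongest reply is that a group-by-time label, in a randomised trial with a pre-treatment visit, ordinarily points to the interaction. The interaction is a valid test under randomisation, holds 5% as a single test, and dilutes nothing. That stands. A reader might infer that the plan dilutes the treatment effect as such, but the text supports this only if the group term is the test, and it does not say so. A reader might likewise infer a 10% false-positive rate. That would need either term to count as success, which the wording leaves open and does not state.

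A second reply is that the power comparison favours ANCOVA, by giving it one visit, the full significance level and the peak effect. This also stands in part. With alpha split over two visits (0.025 each), the 3-month ANCOVA has 81% power at ρ = 0.5, equal to the interaction. At ρ = 0.7 it has 94% against 96%. If the effect builds towards 6 months, a 3-month contrast does much worse. So a flat statement that the planned analysis loses power is not supported.

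A third reply is that direction and rough size would be visible from the reported means and SDs. They would, but without an interval for the difference between arms.

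Finally, covariates and the choice of confirmatory term are often left to a statistical analysis plan. That excuses silence about them. It does not excuse the follow-up test that the article does state, which is within groups and does not address the second aim.

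**Conclusion.** The concern holds in a limited form. Whichever ANOVA term is used, and without any assumed figure, the stated analysis does not locate the visit at which the arms differ and leads to within-group tests instead of a between-arm estimate. This rests on one inference: that the three scheduled assessments are the levels of time.

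The consequences for power are conditional. If the group term decides, an effect D becomes 2D/3, or D/3 if present at 3 months only, with power 60% and 20% at 0.5 SD, ρ = 0.5 and 60 per arm. If the interaction decides, there is no dilution. Its power is usually below that of a baseline-adjusted contrast at the visit where the effect is largest: 81% against 88% at ρ = 0.5, and 66% against 81% at ρ = 0.3. For a constant effect there is little or no difference at ρ of 0.7 or above. The ordering reverses if the effect peaks at the visit not chosen (68% against 35% at ρ = 0.5).

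The ANOVA is not invalid. It is an ambiguous and often less efficient answer to the second aim, and the plan should be changed.

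**What to change.** In Statistical analysis, make the primary between-arm analysis of VAS and of ODI a baseline-adjusted comparison at one visit that the sponsor fixes in advance, reported as an estimated difference with 95% CI. Use ANCOVA, or a mixed model of the 3- and 6-month values with baseline as covariate. The end of treatment at 3 months is a natural choice, but the article does not name a primary visit and the decision is the sponsor's.

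Report the contrast at the other visit from the same model as secondary. Replace the within-group t-tests by these between-arm contrasts. Use the same model for the continuous secondary outcomes.

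**Cost:** wording only. VAS and ODI are already collected at baseline, and no visit or patient is added. Because recruitment is under way, the change should be made and dated before outcome data are compared by arm.

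**Downside:** less power than the interaction if the true effect peaks at the visit not chosen, so the choice of visit should be justified by the expected course of the effect.

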### Study design

This is a single-blind randomized controlled trial comparing a WBV exercise with general exercise (Figure 1). A total of 120 patients with chronic LBP will be recruited and investigated from Shanghai Shangti Orthopedic Hospital and Shanghai University of Sport, Shanghai City, China.

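### The named repeated-measures ANOVA defaults to participants with all three visits, so it does not by itself deliver the promised intention-to-treat analysis, which is also wrongly made conditional on loss

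*Protocol article*

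**What the plan says.** The Statistical analysis section of the protocol article names one method for the comparison between arms: "We will use two-way repeated measures analysis of variance", with factors group and time, "to compare the effect of WBV exercise group with the control group, including the primary and secondary outcomes". Assessments are made "before intervention, at 3 months, and at 6 months" (Study design, text under Figure 1), so the time factor has three levels.

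Missing follow-up is addressed by one sentence in the same section: "If subjects are lost to follow-up, an intention-to-treat analysis will be conducted". The abstract has a parallel sentence: "We will conduct intention-to-treat analysis if any participants withdraw from the trial". Both attach ITT to a condition, namely that someone is lost or withdraws.

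The section Withdrawal criteria and management lists adverse effects related to the vibration exercise among the reasons for which a patient may leave, or be asked to leave, the study. The wording concerns leaving the study, not only stopping the exercise.

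The article names no imputation and no mixed model. It also does not say that participants with incomplete data will be excluded.

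**The concern.** Two statements that the article does fix do not fit together. A conventional repeated-measures ANOVA needs a complete row for each participant: baseline, 3 months and 6 months. Someone with a valid 3-month pain score who misses the 6-month visit drops out of the group-by-time analysis altogether, and the observed 3-month score goes too. This happens exactly when there is loss to follow-up, which is the situation for which the article promises ITT.

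The ITT sentence is a problem in its own right. ITT says that participants are analysed in the arm to which they were randomised. It holds with or without loss, and it does not say what value stands in for a missing score. Making it conditional on loss treats it as a missing-data remedy and leaves the rule unstated for a trial in which nobody is lost but some do not adhere.

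What is at stake is mainly bias. One listed reason for leaving the study can arise only in the vibration arm. If those who leave tend to have more pain, the completers in that arm are a selected group, and a contrast restricted to completers no longer has the protection of randomisation.

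**Working it through.** **No figure in the plan to reproduce.** The article gives 120 participants ("A total of 120 patients with chronic LBP will be recruited"), 1:1 allocation and a significance level of 0.05. It gives no effect size, SD, power or dropout rate. Everything below that needs one of these is an illustration on stated assumptions.

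**Inputs from the article.** N = 120, hence 60 per arm; three assessments; α = 0.05, taken as two-sided because the article does not say.

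**Assumptions.** 10% miss the 3-month visit and 15% miss the 6-month visit; 80% power; a two-sample t-test at one visit as an approximation to the contrast between arms.

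**Step 1: who remains in the ANOVA.**
- Observed at 3 months: 120 × 0.90 = 108.
- Observed at 6 months: 120 × 0.85 = 102.
- Complete at all visits, monotone loss (everyone missing at 3 months is also missing at 6): 120 × 0.85 = 102.
- Complete at all visits, independent losses: 120 × 0.90 × 0.85 = 91.8, about 92.

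**Step 2: detectable standardised difference.** This is approximately d = (1.96 + 0.84) × √(2/n), with n per arm. At n = 60 the formula gives 0.511; the t-distribution raises it slightly, to 0.516. The t-based values are:

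| Participants | n per arm | Detectable d |
|---|---|---|
| 120 (no loss) | 60 | 0.516 |
| 108 | 54 | 0.544 |
| 102 | 51 | 0.560 |
| 92 | 46 | 0.590 |

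**Step 3: what deletion itself costs.** The fair comparator is the number observed at the visit, not 120, because no method recovers scores that were never measured.
- Monotone loss, 3 months: 102 instead of 108, so 0.560 − 0.544 = 0.016 SD.
- Monotone loss, 6 months: 102 either way, so no cost.
- Independent losses, 3 months: 92 instead of 108, so 0.590 − 0.544 = 0.046 SD.
- Independent losses, 6 months: 92 instead of 102, so 0.590 − 0.560 = 0.030 SD.

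A mixed model might recover a little more through the correlation between visits.

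**Step 4: possible bias.** A simulation assumed no true effect, 60 per arm, pain SD of 2 points, correlation 0.5 between visits, and withdrawal before 3 months in the vibration arm only, tending to involve those with worse 3-month pain. The mean difference between arms in change at 3 months was:

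| Withdrawn from vibration arm | All 120 observed | Completers only |
|---|---|---|
| 5% | 0.01 | −0.07 |
| 10% | −0.01 | −0.14 |
| 20% | 0.00 | −0.25 |

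Negative values favour vibration. For scale, on these assumptions the variance of a change score is 2 × 2² × (1 − 0.5) = 4, so the standard error of the difference with 60 per arm is 2 × √(2/60) = 0.37 points. The bias therefore runs from about 0.07/0.37 = 0.2 to 0.25/0.37 = 0.7 standard errors.

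**The case against.** The strongest reply is that this is a journal article, and that the method for missing data is a detail commonly left to the full protocol or analysis plan, neither of which is shown. That is right as far as it goes: the absence of an imputation method is not a finding. Values could be imputed before the ANOVA, or the group-by-time model could be fitted as a mixed model, and the article rules out neither. The ITT sentences also suggest that the authors mean to keep everyone in.

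A reader might therefore be tempted to infer more than the text supports. Three such readings should be set aside:
- That the result is bound to be a complete-case analysis, or that the method cannot yield ITT. The article does not say this. It is the default of the named method, which an added step could change.
- That a participant who misses one visit is lost to every comparison. The planned within-group t-tests can use a change observed at 3 months, and adverse events, the third primary outcome, do not need three complete visits. The group-by-time ANOVA is what is affected.
- That deletion raises the detectable difference from 0.52 to 0.56 SD. Most of that rise comes from scores that were never observed, which no analysis restores.

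It can also be said that the conditional ITT wording is merely loose. Nothing in the article provides for analysis by treatment received, so the wording does not show that anyone would be analysed in the wrong arm.

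What stands is that the article itself fixed the model and fixed a conditional ITT rule, and does not reconcile them. A later document would have to add to or replace the first and correct the second.

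**Conclusion.** The point holds in a limited form. As written, the named ANOVA falls back on participants with all three visits and does not by itself deliver the ITT analysis promised in the abstract and in the Statistical analysis section. The condition attached to ITT is wrong in principle.

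The loss of precision from deletion is small: about 0.02 SD at 3 months under monotone loss, and 0.03 to 0.05 SD under independent losses. These figures rest on assumed dropout of 10% and 15%; the article gives no rate.

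The better reason to act is bias. The withdrawal rule makes arm-related loss plausible, and on the simulation's assumptions a completers-only contrast would favour vibration by about 0.07 to 0.25 pain points when there is no effect. The SD, correlation, dropout share and mechanism are all assumed, so this shows direction and rough size, not a forecast.

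It should be fixed, but it does not by itself undermine the trial.

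**What to change.** Replace the conditional sentence, in the abstract's sense as well, with an unconditional one: all randomised participants are analysed in the arm assigned, whether or not anyone is lost.

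Analyse VAS pain and the ODI with a linear mixed model for repeated measures that uses every available 3- and 6-month value, with group, visit, group-by-visit interaction and the baseline score as terms. A participant seen only at 3 months then still contributes.

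Add a sensitivity analysis for data not missing at random, in which missing values are assumed less favourable than those observed. This is needed because the mixed model does not cure the loss simulated above: those participants leave before any follow-up score, for reasons tied to the unseen score.

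The cost is a different routine in standard software and a little more analysis work. No extra data are required. The article reports that recruitment is underway, so the change should be recorded before outcome data are analysed.
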